### Setting and participants

The trial will be conducted across 20 primary schools in Riyadh city, Saudi Arabia. A list of all governmental primary schools in Riyadh city, Saudi Arabia, will be obtained from the Ministry of Education as the study is stratified based on the area of residence (affluent/non-affluent), and random selection will be conducted. Schools with in-house dental clinics and participating in any dental screening/preventive program will be excluded from the trial.

Children in selected primary schools will be considered eligible to join the trial if they meet all inclusion criteria and none of the exclusion criteria.

Inclusion criteriaChildren aged 8 to 9 years (4th grade at school) at baselineBoth Saudis and non-SaudisChildren for whom the person with parental responsibility has signed the consent/assent form

Exclusion criteriaChildren in 5th and 6th grade (11–12-year-olds) as they would have left schools by the time of the follow-up assessment (18 months later)Children who refuse to participate in the studySpecial need schools are excluded

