#### Primary outcome

The study’s primary outcome is the change in caries experience—the number of decayed (untreated dental caries) missing and filled teeth—in both primary and permanent teeth over 36 months. The underlining assumption of the selected primary outcome is that children in the intervention group will be exposed to more fluoride (toothpaste daily exposure) in addition to mechanical tooth cleaning (correct dental plaque debridement through correct brushing technique) during the trial period leading to a fewer incidence of dental caries than those in the control group.

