### Between groups comparisons

Stata version 17 will be employed for data analysis. In a comparison of demographic (sex, gender), socioeconomic (family income, parental education), behavioral characteristics (tooth brushing frequency, usage of fluoride toothpaste, dental attendance pattern, impact of oral health on daily living, sugar intake), and caries, plaque and gingival level in both primary and permanent teeth, the difference between both intervention groups will be carried out using chi-square test for categorical variables and a *t*-test for continuous variables.

We will be reporting absolute and relative measure effect, that is, absolute and relative difference in mean for continuous outcomes (changes in the number of untreated caries) and risk difference and relative risk for categorical outcomes (changes in brushing frequency, changes in plaque and gingival conditions, changes in impact of oral health on daily living). For the primary outcome (changes in the number of untreated dental caries), negative binomial regression will be used to estimate relative difference (incidence rate ratio) and predictive margin to estimate absolute difference between intervention groups. The applied analytical technique will allow accounting for stratification of the sample and clustering of children within schools and any baseline socioeconomic difference between intervention groups. For the secondary outcome, multinomial regression will be used to estimate relative risk for the changes in frequency of daily tooth brushing and changes in the perceived oral health on child’s daily life. Predictive margins will also be used to estimate absolute difference in each secondary outcome. Intention-to-treat analysis will be used to handle missing values in all outcomes.

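### The primary model is a count regression, but the stated response is a change in caries count that can be negative, and the article names two different primary outcomes

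*Protocol article*

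**What the plan says.** Under Between groups comparisons, the article ties the response to the model in one sentence: "For the primary outcome (changes in the number of untreated dental caries), negative binomial regression will be used to estimate relative difference". On the effect measures, that sentence says that "negative binomial regression will be used to estimate relative difference (incidence rate ratio) and predictive margin to estimate absolute difference between intervention groups". The same paragraph treats this variable as continuous and promises an "absolute and relative difference in mean for continuous outcomes (changes in the number of untreated caries".

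Under Primary outcome, the quantity is different: the "primary outcome is the change in caries experience", meaning decayed, missing and filled teeth, "in both primary and permanent teeth over 36 months". The Abstract and the Discussion agree with that definition. Table 1, like the analysis section, labels the primary outcome as untreated caries.

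The model is said to allow for stratification, clustering and "any baseline socioeconomic difference between intervention groups". The baseline caries count is not named.

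**The concern.** A change is a difference, so it can be negative, zero or positive. Negative binomial regression is for counts, which cannot be negative. If the article means follow-up minus baseline, the only model it names for the primary outcome does not fit the response it names. The analyst would then have to redefine the outcome or change the model once data are in hand, and different repairs can give different answers. The two definitions of the primary outcome add a second open choice: untreated caries responds to treatment uptake, while decayed, missing and filled teeth do not respond in the same way.

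**Working it through.** The article gives no figure on this point to reproduce. The check has four steps.

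**1. Can the change be negative under the stated design?**

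Inputs from the article: age 8–9 at baseline (Setting and participants); primary and permanent teeth over 36 months (Primary outcome); 84% prevalence of untreated caries (sample size section); children with caries in both arms told to book care (Data collection), which is free (Trial interventions).

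| Event between baseline and 36 months | Untreated count | Decayed/missing/filled count |
|---|---|---|
| Decayed tooth is filled | falls by 1 | unchanged |
| Affected primary tooth is shed and no longer counted | falls by 1 if it was untreated | falls by 1 |
| New lesion | rises by 1 | rises by 1 |

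Both counts can fall. The untreated count has two ways to fall, the decayed/missing/filled count only one.

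**2. What does the model do with a negative value?**

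A negative binomial variable has P(Y = y) = 0 for every y < 0. The likelihood is a product over children, so one negative change sets it to zero. The incidence rate ratio is mean(intervention) / mean(control) and needs both means positive. If the mean change in the control arm is zero, the ratio is undefined.

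**3. How many children might be affected?**

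The article gives no mean count, dispersion, shedding rate, treatment rate or incidence, so these inputs are assumptions:
- baseline mean m of 2 to 6 affected teeth, negative binomial with dispersion 1
- proportion r of those teeth lost from the count by 36 months, 10% to 75%
- mean number of new lesions a, 0.5 to 3, dispersion 1, independent of the losses

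Write b = m × r for the mean number lost. The mean change is a − b. With dispersion 1, new and lost teeth both follow geometric distributions, and P(change < 0) = b / (1 + a + b).

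| m | r | a | b | Mean change | P(change < 0) |
|---|---|---|---|---|---|
| 2 | 0.10 | 3 | 0.2 | +2.8 | 0.2 / 4.2 = 0.048 |
| 4 | 0.25 | 1 | 1.0 | 0.0 | 1 / 3 = 0.33 |
| 6 | 0.75 | 0.5 | 4.5 | −4.0 | 4.5 / 6 = 0.75 |

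Simulation with 200,000 children per scenario gave 0.047, 0.334 and 0.751. With 20% dropout, 1192 × 0.80 = 953.6, so about 953 children remain. The lowest scenario gives 953 × 0.048, or about 45 children with a negative change.

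**4. Does the model fit such data?**

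A negative binomial model was fitted to 1192 simulated change scores from the middle scenario, of which 34% were negative. It did not converge and returned undefined coefficients. For the same children, the 36-month count with log(baseline count + 1) as covariate converged normally. These fits left out stratum and school. They illustrate step 2, and the conclusion does not depend on the software.

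**The case against.** The strongest reply is that the article never writes out follow-up minus baseline. The Primary outcome section speaks of a lower incidence of caries, the effect measure is an incidence rate ratio, and there are six examinations. Change could mean newly affected teeth, or a group-by-time effect on repeated counts, and negative binomial regression is valid for either. This stands as a possible intention. A reader might infer that the model fails whatever was meant; the documents do not support that. But they do not state either valid reading, and calling the variable continuous points away from both. This is also not detail left to an analysis plan, because the article itself pairs this response with this model.

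Other points of the reply limit the finding:
- **Shedding.** The article does not mention it or say how shed teeth are coded. A reader might infer a known, large share of negative changes, but the range above rests wholly on assumptions.
- **Treatment.** A reader might infer that free treatment makes either primary outcome fall. It lowers only the untreated count, since a filled tooth stays in the decayed/missing/filled count.
- **Dilution.** A reader might infer that shedding dilutes the effect. That has not been shown. Losses of teeth affected at baseline should be similar in randomised arms, so they add noise but tend to cancel in the absolute difference.
- **Baseline caries.** A reader might infer that baseline adjustment has been ruled out, or that covariates will be picked after imbalance is seen. The wording excludes nothing, and a full covariate list may sit in an analysis plan that is not shown. This is not a separate fault; it matters here only because adjusting for the baseline count is the direct cure.

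**Conclusion.** The point holds for the text as written. The stated response, read literally, lies partly outside the range that the stated model allows, and its rate ratio loses meaning when mean changes are near or below zero. Some negative changes are practically certain given the children's age, the inclusion of primary teeth, the length of follow-up, the high baseline prevalence and free care in both arms. Their share cannot be derived from the documents. The 5% to 75% range depends on the assumed baseline mean, losses and incidence, but the conclusion does not, because a single negative value is enough.

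Separately, and without any assumption, the article gives two different primary outcomes: decayed, missing and filled teeth in the Abstract, Primary outcome section and Discussion, and untreated caries in the analysis section and Table 1. These must be reconciled, since the choice decides whether treatment uptake moves the primary result.

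**What to change.** State one primary outcome and use it throughout the article, including Table 1 and the analysis section. Then make the response a non-negative count.

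- **Simplest form.** Model the 36-month count by negative binomial regression, with trial group and baseline count as covariates, keeping affluence stratum and school clustering. The rate ratio then compares expected 36-month counts at equal baseline, and predictive margins still give the absolute difference. This uses examinations already scheduled and supplies the baseline adjustment that the analysis section does not name.
- **Alternative, if tooth-level records are kept.** Pre-define a count of newly affected teeth, with a stated rule for shed primary teeth and with log teeth at risk as offset. The article does not say that records are kept by tooth, so this must be confirmed first.

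The cost is revised wording and a little more analysis work. The second option also needs tooth-level data entry.

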### Data analysis justification of sample size

Sample size was calculated based on the prevalence of untreated dental caries (84%) reported in a previous study by Adam and his colleagues (2022) among Riyadh children [31]. Considering a 95% confidence interval and 80% power, 690 children (354 individuals per arm) were sufficient to detect a clinically significant difference of 10% with design effect of two arms over a period of 36 months. The design effect was calculated as 1.44, based on an intra-class correlation coefficient of 0.02 derived from a previous study [32]. After accounting for clustering, the required number of clusters would be 20 schools and an average cluster size of 50 participants. Allowing for up to 20% dropout rate upon follow-up time, 1192 participants are required (596 per arm) [33].

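### The 80% power rests on normal quantiles although only 20 schools are randomised: a test held to 5% has about 75% power at the nominal design, and the analysis section names no small-sample method

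*Protocol article*

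**What the plan says.** *Protocol article, Data analysis justification of sample size.* The starting point is a prevalence of untreated caries of 84% and a difference to detect of 10%, not labelled relative or absolute. The claim reads "Considering a 95% confidence interval and 80% power, 690 children (354 individuals per arm) were sufficient". Clustering enters through one factor: "The design effect was calculated as 1.44, based on an intra-class correlation coefficient of 0.02". The section then states that "the required number of clusters would be 20 schools and an average cluster size of 50 participants", and 20% dropout brings the total to 1192 (596 per arm). It prints no allowance for the small number of clusters.

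*Study design and setting; Setting and participants; Randomization; Data collection.* There are 20 schools, allocated 1:1 within two strata (affluent and less affluent). Twenty supervising hygienists at two per school confirm 10 intervention schools.

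*Between groups comparisons.* The primary outcome is analysed by negative binomial regression in Stata 17, and "The applied analytical technique will allow accounting for stratification of the sample and clustering of children within schools". The section does not say whether this means cluster-robust standard errors, a random effect or a survey estimator, nor whether tests and intervals use a z or a t reference.

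**The concern.** A design effect corrects the variance of the arm difference. It does not correct the reference distribution. With schools randomised, the between-school variance that drives the standard error is estimated from 20 units less the fitted terms: 18 df with arm only, 17 df with arm and stratum. Normal quantiles treat that variance as known.

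Two things follow. If the test is properly held to 5%, the power is lower than the 80% printed. If it is not, because z inference is applied to 20 schools without correction, intervals are too narrow and an ineffective programme is declared effective more often than 5% of the time. The Discussion says a positive result would support continuing the programme in many schools, so both errors bear on the decision the trial is meant to inform.

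**Working it through.** **Inputs from the article.** Control prevalence 0.84; difference 10%; 80% power; 95% confidence (two-sided assumed); design effect 1.44; ICC 0.02; 20 schools, about 50 children each; 1192 recruited; 20% dropout.

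**1. Reproduce the printed figure.** Formula: n per arm = (z₀.₉₇₅ + z₀.₈₀)² × [p₁(1−p₁) + p₂(1−p₂)] / (p₁−p₂)².

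- Relative 10% (p₂ = 0.756): (1.960 + 0.842)² × (0.1344 + 0.1845) / 0.084² = 7.849 × 0.3189 / 0.007056 = **354.7**. This matches the printed 354.
- Absolute 10 points (p₂ = 0.74): 7.849 × 0.3268 / 0.01 = 257. A pooled variance gives 260, and a continuity correction 279. None matches.

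So the printed 354 is a normal-quantile figure under the relative reading. (The printed total of 690 is 2 × 345, not 2 × 354 = 708, and 345 × 1.44 × 1.2 = 596.2 leads to the final 596. That is a separate discrepancy and does not drive this point.)

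**2. Power with a t reference.** Noncentrality = 0.084 / √(0.3189 × 1.44 / n). Power is taken from the noncentral t at the two-sided 5% critical value (2.101 on 18 df, 2.110 on 17 df).

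| Design, design effect 1.44 | Noncentrality | z | t, 18 df | t, 17 df |
|---|---|---|---|---|
| Nominal (exactly 80% by z) | 2.80 | 80.0% | 75.5% | 75.2% |
| 500 per arm (20 × 50) | 2.772 | 79.2% | 74.6% | 74.3% |
| 477 per arm (1192 × 0.8 / 2) | 2.707 | 77.3% | 72.6% | 72.3% |

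The change of reference distribution costs about 5 points in each row.

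**3. The printed design effect.** With ICC 0.02, a design effect of 1.44 implies 1 + 0.44/0.02 = 23 children per school. Fifty per school gives 1 + 49 × 0.02 = 1.98, and 47.7 completers per school (953.6/20) gives 1.93. On those values, power on 18 df for 84% vs 75.6% is about 61% (500 per arm, 1.98) and 60% (477 per arm, 1.93). For 84% vs 74% it is about 75% and 74%. This is a different fault from the missing t reference, but a restated power has to settle both.

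**4. Type I error at nominal 5%, by analysis route.** The article gives no mean or dispersion for the count, so the values below are assumptions.

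Analytic approximation, arm and stratum fitted:
- z in place of t alone: P(|T₁₇| > 1.96) = 6.7% (6.6% on 18 df).
- Cluster-robust variance with the usual G/(G−1) factor and z: P(|T₁₇| > 1.96 × √(17/19)) = 8.1%.
- The same variance with t on 17 df: P(|T₁₇| > 2.110 × √(17/19)) = 6.2%.

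Null simulation of a negative binomial model: mean 2.9, dispersion 1 (held at its true value in fitting), ICC 0.02, 48 children per school, two strata, 3000 replicates per scenario:

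| Route | Equal sizes | School-size CV 0.4 | CV 0.4 plus two covariates |
|---|---|---|---|
| Cluster-robust, z | 8.2% | 9.2% | 9.5% |
| Cluster-robust, t on 17 df | 6.3% | 7.1% | 7.2% |
| School-level regression with stratum | 4.7% | 5.8% | 5.4% |

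Further runs with mean 2–3, dispersion 0.5–1 and 40–50 children per school gave 8.0–8.8% for cluster-robust z. A random-intercept maximum-likelihood Wald z test (normal approximation to school means, ICC 0.02) gave 8.2–8.4%. A survey-linearised variance with t on 18 df gave about 6.6%.

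**The case against.** **The analysis section does not commit to z inference.** A reader might infer that the model as written yields 8–9% false positives. The article does not support that. It names neither the variance estimator nor the reference distribution, and its mention of sample stratification and clustering would fit a survey-type analysis with a t reference, which ran at about 6.6%. Small-sample corrections are also commonly left to a statistical analysis plan, which is not shown. This objection stands: the inflation depends on an uncorrected analysis, and the article's silence is not in itself an error.

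**The 75% is not the power of the primary test.** It comes from comparing two prevalences, while the primary analysis models a count. This also stands. No mean or dispersion is printed, so the power for the count outcome is unknown.

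**Under an absolute reading the problem disappears.** For 84% vs 74% with design effect 1.44, power on 18 df is 85% at 477 per arm and 87% at 500. The arithmetic is right, but that reading gives 257–279 per arm and cannot be the source of the printed 354.

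**The design-effect discrepancy is larger.** At 477 per arm, moving from 1.44 to 1.93 costs about 13 points by z (77.3% to 64.7%), against about 5 for the t reference. True, and it means a restatement that kept 1.44 would print another unreliable figure. It does not remove the 5 points, which remain whatever design effect is used.

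The printed 80% survives none of this. A later analysis plan that restored a 5% test would confirm the lower power rather than rescue the claim.

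**Conclusion.** The point holds for the stated power and holds conditionally for the type I error.

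- *Power.* With the printed design effect accepted, a test held to 5% on 20 schools has about 75% power at the nominal design and 72–73% after the planned dropout, against 80% printed. This rests on a two-sided test, the relative reading that reproduces 354, and 17–18 df. It describes the prevalence comparison used for sizing only.
- *Type I error.* If the negative binomial model is run with uncorrected cluster-robust or maximum-likelihood random-intercept z inference, the error rate would be about 8–9%. With a t reference but no variance correction it would be about 6–7%. These figures depend on the assumed mean, dispersion and school sizes, and they describe possible implementations, not what the article prescribes.

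**What to change.** In *Data analysis justification of sample size*, restate the power using a t distribution on 17–18 df. Use a design effect that agrees with the printed ICC and cluster size, and say whether the 10% is relative or absolute.

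In *Between groups comparisons*, specify that the primary arm effect and its 95% interval will come from one small-sample method suited to 20 schools. Suitable choices are:

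- a bias-corrected cluster-robust variance with t on 17 df (20 schools − 2 strata − 1);
- a two-stage school-level analysis: fit the negative binomial model without arm, form observed/expected ratios per school, and compare arms adjusted for stratum on 17 df;
- a permutation test of arm within strata, with the interval from the same procedure.

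The cost is a sentence of analysis wording and a revised power statement, with no extra children or schools. Intervals become slightly wider: the critical value rises from 1.96 to 2.11, a factor of 2.11/1.96 = 1.08, plus any variance correction. The stated power falls by about 5 points for the t reference alone, and further once the design effect is reconciled.

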### Blinding

Children participating in this study cannot be blinded given the nature of the intervention. Both children and their parents will be provided an information sheet that explains the intervention thus will know whether they will be in either intervention or control group. Examiners will be blinded as children in both groups will be dealt with identically in the examination appointment. All outcome assessment data will be delivered to the principal investigators, and thus, each child will be identified to the allocated group according to the child’s code and school code. It is worth mentioning that we chose the caries experience to be the primary outcome as clinical outcomes are considered an objective finding and thus more reliable and less prone to measurement bias associated with subjective self-reported measures.

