## Discussion

Despite the availability of free dental services in Saudi Arabia, dental caries is still a common disease among children. Many studies have focused on the implementation of school-based programs to promote and tackle the burden of untreated dental caries [34]. This study will take a step further and explore the effectiveness of virtual supervised tooth brushing on untreated dental caries especially since Saudi Arabia has proven to have an effective IT infrastructure for virtual schooling.

Three different outcome measures are used to evaluate the effectiveness of virtual supervised tooth brushing on caries experience. The study’s primary outcome is the change in caries experience—the number of decay (untreated dental caries) missing and filled teeth—in both primary and permanent teeth over 36 months (baseline, + 3 months,+ 6 months + 12 months,+ 24 months, + 36 months from baseline) using the WHO criteria [29]. The secondary outcome will be obtained through both clinical outcomes (plaque and gingival scores) and the self-reported questionnaire to assess the change in the frequency of brushing per day and the impact of oral health on the child’s daily life (QoL) [29]. The selected study design will collect data on participants’ socioeconomic and behavioral factors which will help accounting for baseline differences between the two trial groups.

The findings of this study will provide important information on the impact of virtual supervision on dental caries. A positive impact will be an opportunity for targeting a large portion of the population with a high level of disease as a quarter of the Saudi population is younger than 15 years [1]. A positive finding will also support the continuation of virtual supervised tooth brushing in many schools in other parts of the country. Finally, future research should also investigate the factors that could affect the effectiveness of programs. A national study could provide more details about the effectiveness of the program in many different parts of the country.

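### The wording lets socioeconomic adjustment of the primary model depend on observed baseline imbalance; a fixed covariate set would keep nominal error and avoid a possible loss of power

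*Protocol article*

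**What the plan says.** The protocol article's section on between-group comparisons does two things in sequence. It first compares the arms on demographic, socioeconomic, behavioural and clinical variables, where "the difference between both intervention groups will be carried out using chi-square test for categorical variables" and a t-test is used for continuous ones. Family income and parental education are the two socioeconomic variables named. No allowance for clustering is stated for these tests.

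It then gives the primary analysis: "negative binomial regression will be used to estimate relative difference (incidence rate ratio"), with predictive margins for the absolute difference. On adjustment it says "The applied analytical technique will allow accounting for stratification of the sample", together with "clustering of children within schools and any baseline socioeconomic difference between intervention groups". No model terms are listed and no threshold is given.

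The Discussion repeats the rationale: the design collects data on "socioeconomic and behavioral factors which will help accounting for baseline differences between the two trial groups". The Blinding section says outcome data go to the principal investigators and that "each child will be identified to the allocated group according to the child’s code and school code".

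**The concern.** Both statements about adjustment give a between-arm difference as the reason for it. Neither mentions how strongly a variable predicts caries. In a randomised trial a baseline difference between arms is chance, and a test of it says nothing about whether adjusting will sharpen the estimate. A variable that is balanced but prognostic is worth including; one that is imbalanced but unrelated to caries is not.

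Two features of this trial sharpen the point. Schools are randomised, and income and education are likely to cluster by school, so a test that treats children as independent will flag differences far more often than 5% of the time under correct randomisation. Also, a between-arm difference can be seen only with the allocation in hand. The terms in the primary model, and so the incidence rate ratio, could then be settled after the data by arm have been examined. With only 20 schools, any precision given up is hard to recover.

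**Working it through.** **Plan figures.** The article gives no error rate or power for its adjustment strategy, so there is nothing of that kind to reproduce. The total sample size does reproduce: 690 × 1.44 × 1.20 = 1192.3, stated as 1192. Over 20 schools that is 1192 / 20 = 59.6 children per school.

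**How often a child-level test flags a difference.** For a variable with school intraclass correlation ρ (residual to the affluence stratum), ignoring clustering understates the variance by 1 + (59.6 − 1)ρ. A nominal 5% test then flags with probability 2 × [1 − Φ(1.96 / √(1 + 58.6ρ))]:

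- ρ = 0.05: √3.93 = 1.982, 1.96 / 1.982 = 0.989, probability 0.32
- ρ = 0.10: √6.86 = 2.619, 1.96 / 2.619 = 0.748, probability 0.45
- ρ = 0.20: √12.72 = 3.567, 1.96 / 3.567 = 0.550, probability 0.58

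The values of ρ are assumptions.

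**What adjusting only on imbalance does.** Simulation of 20 schools × 50 children in two strata, with outcome ICC 0.02 (the article's value) and 4000 replicates per setting. The following are assumptions:

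- two socioeconomic covariates with school ICC 0, 0.05 or 0.15
- slopes of 0.2 or 0.4 SD each
- an effect of 0.27 SD, set so that always adjusting has about 80% power
- a p < 0.05 threshold for entering a covariate
- a Gaussian outcome, tested at school level with 17 degrees of freedom, in place of the negative binomial model

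With two covariates and unit residual variance, the slopes correspond to 2 × 0.2² / (1 + 2 × 0.2²) = 7.4% and 2 × 0.4² / (1 + 2 × 0.4²) = 24.2% of outcome variance within the model.

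| Covariate ICC | Slope | At least one flagged | Error: always | Error: if imbalanced | Power: always | Power: if imbalanced | Loss (points) |
|---|---|---|---|---|---|---|---|
| 0 | 0.2 | 10.0% | 4.5% | 4.6% | 80.8% | 79.7% | 1.1 |
| 0 | 0.4 | 10.0% | 4.5% | 4.6% | 80.8% | 76.0% | 4.8 |
| 0.05 | 0.2 | 51.2% | 4.7% | 4.2% | 80.6% | 77.8% | 2.8 |
| 0.05 | 0.4 | 51.2% | 4.7% | 3.0% | 80.6% | 68.7% | 11.9 |
| 0.15 | 0.2 | 75.2% | 4.7% | 3.9% | 80.3% | 75.2% | 5.1 |
| 0.15 | 0.4 | 75.2% | 4.7% | 2.5% | 80.3% | 61.5% | 18.8 |

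The Monte Carlo standard error is about 0.3 points for error and 0.7 for power.

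A second simulation used 48 completers per school, covariates explaining 5–10% of the outcome, residual ICC 0.01 and an effect of 0.22 SD. Adjusting if imbalanced gave error 3.6–4.7% and power 71–75%, against power of 77–80% for always adjusting.

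**Why the error falls.** Adjustment is applied in just those replicates where imbalance would have pushed the estimate furthest. In the others the standard error still carries the covariate's between-school noise.

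**The case against.** The strongest reply is that no selection rule is written. The sentence describes what the technique makes possible. Stratification and clustering stand in the same list, and nobody would read those as conditional on a test. Since only two socioeconomic variables are named, always adjusting for both is a possible reading. The comparison sentence does not contain the word baseline, covers variables that are also outcomes, and does not say that its p-values feed the regression. All of this stands: a reader might infer a stated test-then-adjust procedure with a 5% threshold, and the article does not support that.

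A second reply is that the exact covariate list belongs in an analysis plan. That would answer a complaint about a missing list. It does not answer this point, because the article does state a reason for adjusting, and an analysis plan that followed it would inherit the problem.

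A reader might also infer that behavioural items, reported by parents who know the arm, will enter the primary model. The analysis section limits the adjustment to socioeconomic differences, the Discussion sentence is general, and Table 1 marks behavioural data at enrolment, before allocation, as well as at month 0. That inference is not supported.

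Finally, the power figures rest on inputs that the article does not give and on a stand-in for the planned model. That is correct; the direction is firmer than the size.

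**Conclusion.** The point holds as a defect of wording with a real consequence under its natural reading. The text makes imbalance the ground for socioeconomic adjustment and can be read as letting the model depend on differences seen with allocation known.

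Under that reading, type I error is nominal to conservative, about 2.5–4.7%, and power is about 1 to 19 points below always adjusting. With covariates explaining some 7% of the outcome the loss in the table is 1 to 5 points; the upper end needs about 24% together with marked clustering by school. If income and education do not cluster by school, error cannot be told from that of always adjusting and the loss is 1 to 5 points. In no setting examined did adjusting on imbalance beat always adjusting.

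It would be wrong to conclude that the trial risks extra false positives, since every error rate for this strategy was below 5%. It would also be wrong to conclude that covariates would be picked on outcome results: the wording concerns baseline differences only. If the authors already intend to adjust for both variables in all cases, the change only makes that clear.

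**What to change.** Replace the phrase about baseline socioeconomic differences with a named set that enters the primary model whatever the baseline balance: affluence stratum, family income, parental education and the child's baseline caries count. The baseline count goes beyond the socioeconomic sentence and was not part of the simulations; it is included as the starting value of the outcome itself. Present baseline characteristics by arm descriptively, and state that between-arm baseline tests will not be used to choose covariates.

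This takes a few sentences and no new data, since the questionnaire, the baseline examination and the stratification already supply every variable. The one cost is that parent-reported income or education will sometimes be missing. The article's missing-data sentence covers outcomes only, so a simple rule for missing covariates should be fixed in advance so that children are not dropped from the primary analysis.
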